## Methods

### Objectives of the study

The primary objectives of the study are to assess whether the HERrespect intervention reduces female garment workers’ experiences of: (i) physical, sexual, and physical and/or sexual intimate partner violence and (ii) workplace violence in Bangladesh.

Additionally, the study will assess whether HERrespect is effective in: (1) increasing gender equitable attitudes, self-esteem, and knowledge and uptake of services for addressing IPV among female garment workers; (2) reducing acceptance of VAWG and the rate of depression among female garment workers; (3) increasing gender equitable attitudes and knowledge regarding laws and policies addressing gender discrimination and workplace violence against women among management; and (4) improving management styles and attitudes towards workers among management.

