The ten secondary outcomes are being assessed, reflecting hypothesised pathways of change leading to the primary outcomes. Four secondary outcomes focus on gender attitudes and responses to violence:Acceptance of VAWG amongst female garment workers: Acceptance of VAWG among female garment workers is being measured using statements adapted from the Gender Equitable Men (GEM) scale [25] and WHO multi-country study on women’s health and domestic violence against women [26].Gender equitable attitudes of management staff: Gender equitable attitude of the management staff is being measured using statements adapted from the GEM scale [25], WHO multi-country study on women’s health and domestic violence against women [26] and the South African study on men, masculinities, violence and HIV [27].Response to IPV amongst female garment workers: A single item explores women’s help seeking in response to IPV. The question heavily drew upon the WHO multi-country study questionnaire [26] and the SAFE questionnaire [28]. This question will only be asked to those who experienced physical and/or sexual violence during last 12 months.Knowledge of services in response to IPV amongst female garment workers: One question assesses the knowledge of the workers about where to seek help after experiencing IPV.

Two secondary measures assess women’s well-being:5.Self-esteem of female garment workers: The Rosenberg Self-Esteem scale is being used to measure self-esteem [29]. It measures global self-worth by measuring both positive and negative feelings about self. The scale is uni-dimensional and has shown strong convergent validity for men and women from different ethnic groups [30].6.Depression among female garment workers: Depression in the past week is being measured using the Center for Epidemiologic Studies Depression (CES-D) scale used widely in different settings (including Bangladesh) and showing high reliability and validity [31]. Each question is a statement and asked the respondent to answer how many days she has had particular feelings or ideas.

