Severe physical and/or sexual IPV during past 12 months	Questions asked for measuring physical and sexual violence during past 12 months	Never, once, few, many	10	–	–	Binary - never compared to once or more	Decrease
Witnessed or experienced workplace violence	In the past four weeks, how often have you experienced or witnessed a manager call a worker names?	Never, once, 2-3 times, many times	8	0.83		Mean	Decrease
Secondary outcomes							
Gender attitudes and responses to violence							
Acceptance of VAWG among female workers	In your opinion, does a man have good reason to hit his wife if she disobeys him?	4-point Likert: Strongly disagree, disagree, agree, strongly agree	6	0.69	–	Mean	Decrease
Positive gender attitudes among management staff	I think that a woman needs her husband’s permission to do paid work.	4-point Likert: Strongly disagree, disagree, agree, strongly agree	13	–	0.68	Mean	Decrease
Response to IPV	Did you go to any person/place for help when you experienced any physical or sexual violence during last 12 months?	Yes, no	1	–	–	Binary – yes compared to no	Increase
Knowledge of services in response to IPV	Do you know from where one can get help for such experience? If yes, where?	Yes, no	1	–	–	Binary – yes compared to no	Increase
Women’s well-being							
Self-esteem of the female garment workers	At times, You think you are no good at all.	4-point Likert: Strongly disagree, disagree, agree, strongly agree	10	0.76	–	Mean	Increase
Depression among female garment workers during past week	During the past week you thought your life had been a failure.	Rarely or none of the time; some or a little of the time; moderate amount of time; most or all of the time	13	0.87	–	Mean	Decrease
Management knowledge, practices and experiences							
Better management style of management staff	If you do not comply with your supervisor, you will not be rewarded	Very unlikely; Somewhat likely; Very likely	14	0.90	–	Mean	Increase
Correct knowledge regarding laws and policies	Are there laws/policies in this country that protect women from spousal violence?	Yes; no; don’t know	5	–	–	% correct compared to % incorrect	Increase
Positive attitudes regarding laws and policies	To your opinion - “Sexual remark and gesture is an act of workplace violence”	Strongly agree; agree; no opinion; disagree; strongly disagree	5	–		Mean	Increase

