### Sample size

For the worker survey, the sample size calculation was based on the primary outcome – physical IPV against female garment workers. Expecting 56% baseline prevalence of past year physical IPV experienced by the female garment workers (icddr,b unpublished data), and anticipating a 20% effect size, 5% level of significance and 80% power, the required sample size was 330 workers for both the intervention and control groups. To account for a 20% lost to follow up the sample size increased to 396 workers for both the groups, which was rounded up to 400. Thus, a sample of 100 workers would be required from each of the intervention and control factories, giving 800 in total.

For the management survey, the sample size calculation was based on gender inequitable attitudes among garment management staff. Anticipating 50% baseline prevalence of high or moderate gender equitable attitudes among the management staff, a 30% effect size, 5% level of significance and 80% power, the required sample size was 183 management staff for both intervention and control groups. Anticipating 10% loss to follow up, the sample size increased to 200 for both the groups. Thus a sample of 50 management staff would be required from each of the intervention and control factories, giving 400 in total.

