### Statistical methods: Data analysis

Intention-to-treat (ITT) analysis will be used for assessing the impact of HERrespect. Thus, all the workers selected for the study will be included in the analysis. The primary analysis will involve comparison between intervention and control factories for assessing the impact of full HERrespect intervention (group sessions and factory-wide mobilization) over control. First the data from intervention and control factories and baseline and endline samples will be compared and Chi-square (for categorical variables) and t-tests (for continuous variables) will be performed to test whether there are differences in prevalence of background characteristics. If differences between intervention and control factories and baseline and endline samples are evident, the pre-existing differences will be controlled in subsequent analyses. The impact of HERrespect intervention on main outcomes of interest will be assessed using risk ratios derived from binary regression analyses adjusting for baseline rates. All analyses will be adjusted for the potential factors associated with the outcomes of interest. The same approach will be followed for assessing the secondary outcomes.

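### Help-seeking is measured only among women who report IPV at endline, a group formed after the intervention by the outcome it targets, so the between-arm comparison should be descriptive

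*Protocol article*

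**What the plan says.** The Trial outcomes section of the protocol article defines Response to IPV by one item and restricts who answers it: "This question will only be asked to those who experienced physical and/or sexual violence during last 12 months". Table 2 gives the item, "Did you go to any person/place for help when you experienced any physical or sexual violence during last 12 months", scores it as a binary yes against no, and hypothesises an increase.

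The restricting event is what the programme is meant to change. Under Objectives of the study, "The primary objectives of the study are to assess whether the HERrespect intervention reduces" is followed by physical and sexual IPV. Uptake of services for IPV is a separate, additional objective, and this item is the only listed outcome that measures it; outcome 4 measures knowledge.

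Participant timeline has the intervention finishing in August 2017 and the endline running from September to November 2018.

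Statistical methods: Data analysis specifies intention to treat, so that "all the workers selected for the study will be included in the analysis". It plans risk ratios adjusted for baseline rates and extends the same approach to the secondary outcomes, with no exception for this one.

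**The concern.** A woman interviewed at endline enters the help-seeking denominator only if she reports IPV from a period after the intervention ended. If the programme prevents some violence, the intervention-arm denominator loses those women and the control-arm denominator keeps their counterparts. The two proportions then describe differently selected groups.

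Disclosure is a second route. Entry depends on reported violence, nobody is blinded, Limitations concedes possible under-reporting, and the programme addresses the normalisation of violence. A change in reporting alone would change who is asked.

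Adjustment for baseline characteristics does not remove a selection that arises after the intervention. At stake is the conclusion on service uptake: the programme could be credited with an increase it did not cause, or appear to reduce help-seeking when it did not.

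**Working it through.** **Inputs from the Sample size section.** The starting rate is given as: "Expecting 56% baseline prevalence of past year physical IPV experienced by the female garment workers". The planned effect is 20%, tested at the 5% level with 80% power. The result before allowing for loss is that "the required sample size was 330 workers for both the intervention and control groups". A 20% allowance for loss then takes the figure to 396 per arm.

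**Plan's own figure.** Read the 20% as relative: 0.56 × 0.80 = 0.448, a fall of 11.2 points. The two-sided 5%, 80% power formula for two proportions gives 312 per arm, and 330 with the continuity correction, which matches the plan. 330 × 1.2 = 396, rounded up to 400. The relative reading is therefore the one the plan used. No figure is given for the help-seeking outcome.

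**Timing.** The earliest endline interview, in September 2018, looks back to September 2017. The intervention ended in August 2017, so the whole recall window follows it.

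**Who would be asked.** With 20% loss, 400 × 0.80 = 320 per arm. Control: 320 × 0.56 = 179. Intervention: 320 × 0.448 = 143. These are approximate, because 56% is physical IPV only and the item goes to women with physical and/or sexual IPV, a group that cannot be smaller.

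**General form.** Suppose no woman's help-seeking changes and IPV is only prevented, never caused. Let *h* be the help-seeking rate in persisting cases and *g* the rate that prevented cases would have had.

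- Intervention proportion = *h*
- Control proportion = (0.448*h* + 0.112*g*)/0.56 = 0.8*h* + 0.2*g*
- Spurious difference = 0.2(*h* − *g*), which is zero when *h* = *g*

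Assumed values (the documents give none):

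| *h* | *g* | Control | Intervention | Risk ratio |
|---|---|---|---|---|
| 30% | 30% | 30% | 30% | 1.00 |
| 30% | 10% | 26% | 30% | 1.15 |
| 30% | 0% | 24% | 30% | 1.25 |
| 20% | 40% | 24% | 20% | 0.83 |

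**Illustration by severity.** Assume control has 20% severe IPV (40% seek help) and 36% milder IPV (10% seek help). Control help-seeking among reporters = (0.20×0.40 + 0.36×0.10)/0.56 = 0.116/0.56 = 20.7%. Now apply the 11.2-point fall:

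- All in milder cases: (0.20×0.40 + 0.248×0.10)/0.448 = 0.1048/0.448 = 23.4%, or +2.7 points, risk ratio 1.13.
- All in severe cases: (0.088×0.40 + 0.36×0.10)/0.448 = 0.0712/0.448 = 15.9%, or −4.8 points, risk ratio 0.77.
- Proportional (16% severe, 28.8% milder): 0.0928/0.448 = 20.7%, no bias.

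**Whole-cohort view of the same illustration.**

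| | No IPV | IPV, sought help | IPV, no help |
|---|---|---|---|
| Control | 44.0% | 11.6% | 44.4% |
| Fall in milder cases | 55.2% | 10.5% | 34.3% |
| Fall in severe cases | 55.2% | 7.1% | 37.7% |

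The last column moves by −10.1 or −6.7 points with no change in help-seeking. The middle column also falls. Neither column alone isolates help-seeking.

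**The case against.** The restriction looks like a questionnaire skip rule: a woman with no IPV cannot have sought help for it, and the analysis set might be left to an analysis plan that is not shown. It stands that the conditional proportion is a natural quantity to report and that no data are lost, since the whole-cohort breakdown can be built from items already asked. It does not remove the point. The article itself gives this outcome a yes-against-no scoring and a directional hypothesis, and applies the all-workers approach to secondary outcomes.

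The arms are not randomised and already differ at baseline, so every outcome compares different women. That is true and disclosed. Selection on a post-intervention event is an additional problem, one that Limitations does not mention and that the measures offered for baseline differences do not reach.

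Stratifying by severity would remove the bias completely in the illustration above. That also stands, but only because help-seeking was assumed constant within each stratum. Severity is itself measured after the intervention, so such an analysis is supportive only.

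The magnitudes are assumed extremes. This stands in full. The proportional case gives zero, and with about 179 and 143 women the 95% half-width of the difference is about 8.4 to 9.1 points before clustering, wider than either extreme in the severity illustration.

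A reader might infer that the comparison is necessarily biased whenever the programme works. The documents do not support this: prevented and persisting cases must also differ in help-seeking. A reader might also infer that the remedy is to test IPV without help-seeking over all workers. That measure falls whenever IPV falls, so it would largely re-test the primary outcome.

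**Conclusion.** The point holds in a limited form. As defined, the endline comparison of help-seeking conditions on a post-intervention event that is the programme's primary target, and it cannot carry the all-workers intention-to-treat claim. That part rests on the article's own definition, timeline and analysis section. The only inference is that the skip rule applies at endline to the 12 months before interview.

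The size and direction of any bias are unknown. The risk ratios of 0.77 to 1.25 depend wholly on assumed help-seeking rates, an assumed severity split, the planned 20% relative fall, and the physical-IPV figure standing in for physical and/or sexual IPV. If prevented and persisting cases seek help equally often and disclosure is unchanged, the bias is zero. One secondary outcome is affected; the primary IPV outcomes are not, and knowledge of services carries no stated restriction to IPV reporters.

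**What to change.** In Trial outcomes, Table 2 and Statistical methods: Data analysis, state that the proportion seeking help among women reporting IPV is descriptive, is exempt from the all-workers intention-to-treat statement, and will not be read as evidence of an intervention effect on uptake of services.

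Beside it, show for all workers by arm the three-way breakdown: no IPV; IPV and sought help; IPV and no help sought. Add a supportive comparison stratified by IPV severity or frequency from the items already collected, with the strata defined in advance. Do not substitute IPV without help-seeking as the tested measure of help-seeking.

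No new question or fieldwork is needed; the change is wording and one table. The cost is that the trial gives up a confirmatory claim on this secondary outcome, which is the only listed outcome for service uptake.

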### Trial design

The trial employs a quasi-experimental design. It is being conducted in four intervention and four control factories. In the intervention factories a randomly selected cohort of married female line workers, a cohort of male line workers, and all middle management staff received the main intervention. In addition, factory-wide campaigns were carried out, and a community activity in one intervention community. For the evaluation, two cohorts have been established and will be followed up over 24 months in each of the intervention and control factories. One is a cohort of randomly selected female line workers (100 per factory) and the second is a cohort of selected management staff with frequent interaction with workers (50 in each factory). Two different questionnaires are administered for workers and management staff (see Additional files 1 and 2). All the workers and management staff from these cohorts were interviewed at baseline, and will be interviewed in the endline. The baseline was conducted before the intervention started, while the endline will be conducted 24 months post-baseline.

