### Trial outcomes

Considering the objectives of the HERrespect intervention, four primary outcomes, split into two groups, were identified:Three primary outcomes are focused on: physical, sexual, and physical and/or sexual IPV experienced by female garment workers in the past 12 months:The proportion of women experiencing any physical IPV from husband during the past 12 months.The proportion of women experiencing any sexual IPV from husband during the past 12 months.The proportion of women experiencing severe physical and/or sexual IPV from husband during the past 12 months.

These outcomes are being measured using a set of questions based on the World Health Organization (WHO) violence against women instruments, which are designed to minimize reporting biases that arise from subjective perceptions of abuse by asking only about specific behaviours perpetrated by a male partner. The questions have been adapted for the “What Works To Prevent Violence against Women and Girls?” Global Programme and are being used across the evaluations within the programme.2.Violence witnessed or experienced at workplace in the past 4 weeks by female garment workers: This outcome is being assessed with an 8-item scale asked to the female garment workers, which was loosely developed as an adaptation of the peer victimisation scale [24]. The adaptation has been to measure ‘experiencing or witnessing’ victimisation as this was deemed to be less sensitive with factory management than actual reported victimisation. The adaptation of questions drew heavily on the findings of the formative research on the types of violence which occur in the work place.

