Four secondary outcomes focus specifically on management knowledge, practices and experiences:7.Management style: An adapted version of the social power scale developed by French and Raven (1959) and revised by Swasy (1979) is being asked to the female garment workers for measuring management styles of the managers [32, 33].8.Knowledge regarding laws and policies: The management staff are being asked five questions for assessing knowledge of the management staff on gender rights of women and protection of women against IPV and workplace violence guaranteed in laws and policies of Bangladesh.9.Attitudes regarding laws and policies: The management staff are being asked five questions to measure their attitudes regarding the existing laws and policies about protection of women against spousal violence and workplace violence.10.Burn out among management staff: The Maslach Burnout Inventory-Human Service Survey (MBI-HSS) is being adapted for measuring burnout of the management staff in the studied garment factories. The MBI-HSS has four subscales, which are Emotional Exhaustion (nine items); Personal Accomplishment (eight items); Depersonalization (five items); and three Optional items. Together, the subscales of the MBI-HSS provide a three dimensional perspective on burnout. Various studies regarding the MBI-HSS confirmed the soundness of the psychometric properties of the instrument (including variance of factor loadings), as well as its reliability and validity [34].

The summary of the trial outcomes is presented in Table 2.

**Table 2 Tab2:** Primary and secondary outcomes of the trial

	Typical Item	Response categories	Number of items	Cronbach Alpha for Worker data	Cronbach Alpha for Management data	Method of scaling	Hypothesis regarding expected change
Primary outcomes							
Physical IPV during past 12 months	In the past 12 months, how many times your current husband has slapped you or something to you that could hurt you?	Never, once, few, many	5	–	–	Binary - never compared to once or more	Decrease
Sexual IPV during past 12 months	In the past 12 months, how many times your current husband has physically forced you to have sexual intercourse when you did not want to?	Never, once, few, many	5	–	–	Binary - never compared to once or more	Decrease

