### Eligibility criteria

Workers were eligible for the research if they were currently married and living with husband (necessary for measuring IPV) and had been working in the current factory for at least one year. All management staff in the factory management were eligible to participate in the study.

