### Endline survey

Similar strategy from the baseline survey will be followed during the endline survey.

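### The IPV items shown in Table 2 name only the current husband, so if used as printed at 24 months they would miss past-year violence by a husband the woman has since left

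*Protocol article*

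**What the plan says.** The Trial outcomes section of the Protocol article defines the first primary outcome as "The proportion of women experiencing any physical IPV from husband during the past 12 months". The sexual and the severe physical and/or sexual outcomes are framed in the same way, with the husband as perpetrator and no restriction to the present one. The same section describes the instrument as "asking only about specific behaviours perpetrated by a male partner".

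Table 2 gives one example item for each type of violence. The physical item opens "In the past 12 months, how many times your current husband has slapped you". The sexual item reads "In the past 12 months, how many times your current husband has physically forced you to have sexual intercourse when you did not want to". The third IPV outcome has no wording of its own; its entry is "Questions asked for measuring physical and sexual violence during past 12 months", ten items in all.

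Under Eligibility criteria, workers had to be "currently married and living with husband (necessary for measuring IPV"; this is a condition of entry. Under Trial design, "the endline will be conducted 24 months post-baseline". The Endline survey section says only "Similar strategy from the baseline survey will be followed during the endline survey". Cohort tracking provides for tracing women who change job or residence, and Statistical methods keeps every selected worker in an intention-to-treat analysis. The article does not say how a woman who is separated, divorced, widowed or remarried at endline is asked or coded.

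**The concern.** At baseline, current husband and husband were almost the same thing, because every woman was living with one. Two years later they need not be. A woman who was hit inside the 12-month window and then left has no current husband to report on, and a remarried woman would report only on the new one. The outcome as defined includes that violence; the item as printed does not ask about it.

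Recorded IPV could therefore fall with no fall in violence. The arms could also be affected unequally. The intervention tells women that violence is never justified and informs them about legal, counselling and shelter services, so leaving a violent husband is a plausible response. The arms also differ in age at baseline (Table 3: 8.3% against 1.3% aged 15-19, and 4.8% against 17.8% aged 35 or over), so separation could differ for other reasons. The secondary outcome on help-seeking is asked only of women reporting past-year violence, so the same women could drop out of it. Violence that was never asked about at endline cannot be recovered in the analysis.

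**Working it through.** **1. The plan's own scale.** Sample size assumes 56% past-year physical IPV and a 20% effect, with 330 per group. Read as a relative effect, 0.56 × 0.80 = 0.448, a difference of 11.2 points. With two-sided 5% and 80% power, and mean proportion 0.504:

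n = [1.960 × √(2 × 0.504 × 0.496) + 0.842 × √(0.56 × 0.44 + 0.448 × 0.552)]² / 0.112² = 312, and 330 with the continuity correction.

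The stated 330 is reproduced, so 11.2 points is the right yardstick.

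**2. What the item loses.** Let s be the share of women who left a husband within the window, and q the share of them abused by him within it. Neither is in the article; I take s from 0 to 10% and q from 56% to 100%. If these women are scored as never, recorded prevalence = true prevalence − s × q. The loss runs from 0.02 × 0.56 = 1.1 points (s = 2%) to 0.10 × 1.0 = 10 points.

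**3. Equal leaving, no true effect.** With q = 0.8 and s = 2%, 5% or 10% in both arms, recorded prevalence is 54.4%, 52.0% or 48.0% in each arm, and the risk ratio stays at 1.00.

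**4. Unequal leaving, no true effect, scored as never.** The last column is the chance of a significant false benefit with 330 per arm, ignoring clustering (nominal 2.5%).

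| Left: intervention vs control | q | Risk ratio | Share of 11.2 points | False benefit |
|---|---|---|---|---|
| 5% vs 2% | 0.56 | 0.97 | 15% | 6% |
| 5% vs 2% | 1.0 | 0.94 | 27% | 12% |
| 10% vs 2% | 0.56 | 0.92 | 40% | 21% |
| 10% vs 2% | 1.0 | 0.85 | 71% | 54% |

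**5. Skipped or scored as never.** Take an extra 5% of intervention women (20 of 400), all abused in the window, and none in control:

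- Skipped: (56 − 5)/95 = 53.7%; 53.7/56 = 0.96. The shift is 2.3 points, or 2.3/11.2 = 21% of the planned difference.
- Scored as never: 51/56 = 0.91. The shift is 5/11.2 = 45% of the planned difference.
- With 3% instead of 5%: 53/97 = 54.6% (ratio 0.98) and 53/56 = 0.95.

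If the leavers had been abused no more often than other women (q = 0.56), skipping them does no harm: (56 − 0.56 × 5)/95 = 56.0%.

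**6. Which departures count.** Participant timeline has the intervention ending in August 2017 and the endline in September to November 2018. The recall window therefore opens between September and November 2017, after delivery ended. For a woman who left during the programme, violence before she left lies outside the outcome under any wording. The loss comes mainly from departures in the year before endline.

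**The case against.** The strongest reply is that the wording is only sampled. The Table 2 column is headed as typical items and shows one of five physical and one of five sexual questions. The worker questionnaire is an additional file that is not shown, and it may hold marital-status filters or items on former husbands. The statement on a similar endline strategy follows sections on teams, tools, fieldwork and quality control; it does not say that every item is repeated word for word. This stands, and it is why the point is conditional on use as printed. It does not remove the mismatch between definition and item in the article itself, where both displayed items agree on the current husband.

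A reader might go further and infer that violence by former husbands is definitely not counted, and that all three IPV outcomes will be biased towards benefit. The article does not support that. It states no coding rule for women without a current husband, so skipped and scored as never are both suppositions. It gives no separation rate by arm. Equal leaving leaves a null risk ratio at 1.00, and a distortion towards benefit needs more such losses in the intervention arm. The timing in step 6 removes most departures during the programme. The figures concern physical IPV only; nothing comparable can be computed for the other two outcomes.

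There is also a fair caution about changing the wording. The questions are shared with other evaluations in the programme, and the analysis adjusts for baseline rates. Eligibility sets no minimum length of marriage, so a few women may already have had a former husband within the baseline window. The remedy should therefore add to the existing items and not replace them.

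**Conclusion.** The mismatch is real. The outcomes refer to the husband over 12 months, the displayed items refer to the current husband, and cohabitation is assured only at entry. If the items are used as printed at endline, recorded IPV will be too low in whichever arm has women who were abused in the window and have since left.

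Bias in the arm comparison is possible, not established. Under no true effect it requires those losses to differ by arm. In the illustration of an extra 5%, all abused in the window, the spurious risk ratio is 0.96 or 0.91 depending on coding; over the wider assumed range in step 4 it runs from 0.97 to 0.85. Every one of these figures rests on leaving rates, abuse rates among leavers and a coding rule that the article does not give. I would rank this as a worthwhile correction before endline, below the defects that must be cured for the trial to be interpretable.

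**What to change.** At endline:

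- Record marital and cohabitation status, and any change since baseline, before the IPV section.
- Keep the current-husband items as they are, for comparability with baseline and with the programme's other evaluations.
- For women whose status has changed, ask the same ten items about any former husband in the past 12 months.
- Score the three IPV primary outcomes as violence by any husband in the past 12 months, for every interviewed woman whatever her marital status.
- Report endline marital status by arm, and add a sensitivity analysis limited to women still with the baseline husband.

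The cost is one filter, a few extra questions for the women concerned, and an endline definition slightly wider than the baseline one. Because the current-husband items are kept, the narrower version can still be reported alongside. If the full questionnaire already covers former husbands, the only change needed is to correct Table 2 and say how these women are scored.
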